## Abstract

**Background:**

Vitamin D deficiency has been linked to poor outcomes after total hip replacement (THR) or total knee replacement (TKR), including lower patient-reported outcome measures (PROMs), peri-prosthetic infection and longer hospital stay. We present a randomised feasibility trial protocol designed to prospectively investigate the influence of vitamin D testing, and subsequent supplementation for deficiency, prior to THR/TKR.

**Methods/design:**

One hundred adult patients undergoing primary THR/TKR for osteoarthritis at two NHS hospital trusts in North East England will be recruited. Exclusion criteria include lack of mental capacity, revision surgery, participants already taking vitamin D/calcium supplements, or a known contraindication to vitamin D treatment. Participants will be ineligible for the trial if they have an estimated glomerular filtration rate < 30 ml/minute. We will measure patients’ vitamin D levels at baseline, and those identified as deficient (vitamin D < 50 nmol/L) will be randomised to receive either vitamin D supplementation or no supplementation prior to, and for 6 months following, surgery. Patients with a normal vitamin D level (≥50 nmol/L) will receive no supplementation. Vitamin D levels will be rechecked on the day of surgery and again at 6 months. Patients will also complete a lifestyle questionnaire, as well as the Oxford hip or knee and EQ-5D-3 L PROM questionnaires, at baseline and at 6 months following surgery. The aims are to determine the feasibility of the methodology and to gather data to inform the conduct of a future, larger trial to investigate if supplementation with vitamin D, in those who are deficient, prior to THR/TKR improves outcomes as measured by PROM scores.

**Discussion:**

Previous reports have measured vitamin D levels and correlated this to outcome, but we can find no randomised trial in which researchers investigated the effect of supplementation. The aim of this trial is to determine if vitamin D deficiency is a modifiable risk factor for poor outcome after THR/TKR.

**Trial registration:**

ISRCTN Registry, ISRCTN14533082. Registered on 3 April 2017.

**Electronic supplementary material:**

The online version of this article (doi:10.1186/s13063-017-2255-2) contains supplementary material, which is available to authorized users.

## Background

The extra-skeletal effects of vitamin D are well documented, affecting almost every cell type through the vitamin D receptor, and deficiency has been linked to a myriad of conditions, including cancer, auto-immune disease, cardio-respiratory disease and depression [1]. The vitamin is synthesised in the skin in response to sunlight; however, for at least 6 months of the year, the United Kingdom is located above the latitude where this can be achieved [2]. Consequently, insufficient levels during the winter and spring months are reported in > 50% of adults over 65 years of age [3].

Vitamin D deficiency has been linked to poorer patient-reported outcome measures (PROMs) following total hip replacement (THR) and total knee replacement (TKR). In 2010, researchers in a study comprising 62 patients reported that those with vitamin D deficiency (25-hydroxyvitamin D [25-OH vitamin D] < 40 nmol/L) had lower Harris Hip Scores before and after surgery than those with a sufficient level (25-OH vitamin D > 40 nmol/L) [4]. A similar result was found in patients undergoing TKR [5]. Shin et al. reported a statistically significant lower Knee Society score, as well as a longer 6-m walk time, following TKR surgery in patients with vitamin D deficiency than in those with a normal level [6].

Lee et al. [7] suggested a link between vitamin D deficiency and post-operative pain. The authors found that, at 3 months following TKR surgery, 13.8% of those patients with pre-operative deficiency were more likely to report ongoing moderate to severe pain than those with sufficient levels (5.9%; *p* = 0.05), and the role of vitamin D in the modulation of anti-inflammatory cytokines was suggested as a possible reason for this.

In a German study of over 1000 arthroplasty patients, vitamin D deficiency was associated with a significantly longer stay following surgery, by 4.3 days (mean 15.6 vs. 11.3 days), even when adjusting for confounders in multivariable analysis [8]. The same authors reported a significantly greater prevalence of vitamin D deficiency in patients presenting at their unit for revision surgery due to peri-prosthetic joint infection, compared with those presenting with aseptic loosening or for primary surgery [9]. Their conclusion, like that of others, is recommendation of a randomised trial to investigate the effect of vitamin D supplementation prior to THR/TKR in a bid to improve outcomes. To date, to our knowledge, no such trial has been performed or registered.

On the basis of National Joint Registry data, 190,000 primary THR/TKR procedures were carried out in England, Wales and Northern Ireland in 2016 [10]. Some patients remain unhappy following joint replacement surgery, with up to 20% of TKR patients reporting dissatisfaction [11, 12], and the origin of a negative outcome may be multi-factorial. PROM scores are measured in the NHS prior to and at 6 months following surgery to assess outcomes following THR/TKR, with financial implications for NHS trusts if they are a negative outlier, defined as 3 SD below the mean PROM improvement. NHS PROMs are currently assessed using the Oxford hip or knee score, as well as the EQ-5D-3 L, a generic measure of health status.

## Methods/design

### Aim

The aim of this prospective, randomised controlled trial is to determine the feasibility of the methodology and to gather data to inform the conduct of a future, larger trial to investigate if supplementation with vitamin D, in those who are deficient, prior to THR/TKR improves outcomes as measured by PROM scores.

### Ethics, consent and permissions

Northumbria Healthcare NHS Foundation Trust is the trial sponsor. The trial will be conducted in accordance with the Declaration of Helsinki. The trial has received a favourable ethical opinion from the Yorkshire and the Humber – Bradford Leeds Research Ethics Committee (17/YH/0067) and has Health Research Authority approval (Integrated Research Application Service 216934). It has National Institute for Health Research portfolio status (Central Portfolio Management System identifier 33969) and was prospectively registered on 3 April 2017 with the International Standard Registered Clinical/soCial sTudy Number (ISRCTN) database (ISRCTN14533082). The current protocol is version 1, dated 31 January 2017, and any changes to the protocol will be communicated to all relevant parties, including patients. We have received charitable funding from Orthopaedic Research UK to support this study.

### Participant recruitment

In this feasibility trial, we will recruit a total of 100 participants from 2 NHS hospital trusts in North East England: Northumbria Healthcare NHS Foundation Trust and South Tees Hospitals NHS Foundation Trust. Participant recruitment was expected to commence by May 2017, and the trial is due to last 20 months. This assumes 2 months for patient recruitment, up to 3 months between recruitment and surgery, 6 months to complete post-operative PROM scores, 6 months for data retrieval and analysis, and 3 months to write the study report. Figure 1 displays the trial schedule, and a Standard Protocol Items: Recommendations for Interventional Trials (SPIRIT) checklist is included as Additional file 1.

**Fig. 1 Fig1:**
[figure not shown]
Standard Protocol Items: Recommendations for Interventional Trials (SPIRIT) checklist. *25-OH Vitamin D* 25-Hydroxyvitamin D

### Eligibility

Participants will be older than 18 years of age and be scheduled for primary THR/TKR performed for a diagnosis of osteoarthritis. Exclusion criteria include participants who lack the mental capacity to comply with study procedures, participants undergoing revision surgery, participants already taking vitamin D supplements, participants with a known contraindication to vitamin D treatment (such as a previous diagnosis of sarcoidosis or hyperparathyroidism), and participants with an allergy to vitamin D. Participants will be ineligible for the trial if they have renal impairment with an estimated glomerular filtration rate (eGFR) < 30 ml/minute.

### Informed consent

Eligible participants will be identified in the outpatient clinic of their treating surgeon once they have been added to the waiting list for surgery. The research team will inform potential participants about the trial and provide them with a patient information sheet. Willing participants will be screened for eligibility by good clinical practice (GCP)-trained research staff, and have the opportunity to ask any questions they may have about the trial, before giving written informed consent for participation (Additional file 2). Patients will be given up to 1 week to make a decision regarding their involvement in the trial; if they are happy to give consent straight away, then this will be allowed. Patients will be free to withdraw from the study at any time without having to give a reason. They will not be eligible to participate in other clinical trials during the study period.

### Baseline assessment

Participants will have routine baseline blood tests performed, including full blood count, urea and electrolytes, eGFR, liver function tests, calcium and albumin, as well as having their serum 25-OH vitamin D level measured. These tests will be analysed pragmatically using the routine laboratory methods available at each NHS Trust hospital. Northumbria use the cobas e 601 Total 25-OH vitamin D immunochemiluminescence assay (Roche Diagnostics International Ltd., Rotkreuz, Switzerland), which has a detection range of 7.5–175 nmol/L and a laboratory-quoted coefficient of variation of 7.7%. At South Tees, the IDS-iSYS 25-Hydroxy Vitamin D^s^ immunoassay (Immuno Diagnostic Systems [IDS], Boldon, UK) is used, which has a detection range of 18–313 nmol/L and a quoted coefficient of variation up to 11.6%.

Patients will also be asked if they give their consent for an extra sample of blood to be taken and stored anonymously at Newcastle University for research purposes only, including in future research trials. Participants will provide basic demographic data and complete a questionnaire regarding diet and lifestyle to assess their exposure to environmental and dietary vitamin D. Whilst we could not find a validated questionnaire to assess diet and lifestyle influences, the questions we will ask are similar to those reported by Lee et al. [13]. Answers will be recorded in the case report form (CRF), and patients will be allocated a trial identifier that does not contain any patient-identifiable data.

As part of their routine care, participants complete baseline PROMs, which are either the Oxford hip or knee score, and the EQ-5D-3 L questionnaires (Appendix 1). These are routine measures collected by the NHS to assess the quality of care experienced by patients undergoing THR/TKR. These questionnaires, which are used to gather routinely collected data, will be obtained for this trial.

### Randomisation

Those participants with vitamin D deficiency (< 50 nmol/L) will be randomised to receive either vitamin D supplementation or no supplementation. Research nurses recruiting participants into the trial will call the research and development (R&D) department at the sponsor site by telephone to obtain the participant’s randomised group allocation. The central R&D administrator will provide this information from a randomisation log generated by the website www.randomization.com. Randomisation will be stratified by study site, and patients will be allocated to either vitamin D supplementation or no supplementation using a 1:1 ratio at both sites. The R&D administrator will provide written confirmation of group allocation using secure nhs.net email.

### Intervention group

Those patients who are randomised to receive treatment will receive oral cholecalciferol according to their vitamin D level. Patients with insufficiency (25–49 nmol/L) will receive 1600 IU/day oral cholecalciferol until 6 months following surgery. Patients with deficiency (< 25 nmol/L) will receive 20,000 IU of oral cholecalciferol twice per week for 8 weeks, then receive 1600 IU/day oral cholecalciferol until 6 months following surgery. Patients’ calcium levels will be re-checked to monitor for hypercalcaemia, and vitamin D treatment will be stopped if this is noted. Patients will not be blinded to their treatment allocation.

### Control groups

Those participants with a normal vitamin D level (≥ 50 nmol/L) will be eligible for inclusion in the trial, but not for randomisation. Along with those patients with vitamin D deficiency who are randomised to receive no supplementation, they will act as control subjects. The control patients will be blinded to their vitamin D status for the duration of the trial and asked not to start taking any supplements containing vitamin D for the duration of their participation in the trial. There are therefore three groups in this trial; patients with vitamin D deficiency who do not receive supplementation, patients with vitamin D deficiency who receive supplementation, and patients with sufficient vitamin D levels. Not providing vitamin D supplementation is current standard practice in the participating NHS trusts, so the control group will, in effect, receive standard care.

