### Statistical analysis

A secure Excel database (Microsoft Inc., Redmond, WA, USA) will be used to record data. Statistical analysis will be performed using IBM SPSS software (IBM, Armonk, NY, USA). We will compare health gain between groups at baseline and at 6 months, as well as mean pre-operative and post-operative PROM scores between groups. Significance will be denoted at *p* < 0.05, and we will report 95% CIs as appropriate. The statistical test chosen to compare groups will depend on the data distribution and the level of the data (nominal, ordinal or interval/ratio). For parametric data comparing two groups, Student’s *t* test for independent samples will be used. The Welch correction will be used if variances are unequal. If the distributions are not normal or the data ordinal, the Mann-Whitney *U* test will be used. The chi-square test or Fisher’s exact test, depending on observed frequencies, will be used for non-parametric data. Paired tests will be used to compare data within participants pre- and post-surgery as appropriate, with tests (e.g., paired *t* test, Wilcoxon signed-rank test) selected depending on the level and distribution of the data as described above. We recognise that outcomes are likely to be confounded with baseline characteristics (e.g., low physical activity levels, age), type of surgery (TKR/THR) and hospital site, and we will investigate the influence of these baseline confounders on outcomes using multivariable modelling (e.g., logistic regression, analysis of covariance). However, given that this is a feasibility study, and it is therefore not fully powered, such multivariable techniques will be used sparingly and only where justified (e.g., sufficient variable-to-participant ratio). The main aim of inferential analysis of clinical outcomes will be to inform a future fully powered study, rather than to draw direct inferences regarding outcomes.

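### Never-randomised vitamin-D-sufficient patients share the control label with the randomised controls, and the between-group comparisons are not tied to the randomised pair

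*Protocol article*

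**What the plan says.** All references are to the protocol article.

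- **Randomisation.** "Those participants with vitamin D deficiency (< 50 nmol/L) will be randomised to receive either vitamin D supplementation or no supplementation", and "patients will be allocated to either vitamin D supplementation or no supplementation using a 1:1 ratio at both sites".
- **Control groups.** Patients at or above 50 nmol/L "will be eligible for inclusion in the trial, but not for randomisation". The next sentence reads "Along with those patients with vitamin D deficiency who are randomised to receive no supplementation, they will act as control subjects". The section then counts three groups: "patients with vitamin D deficiency who do not receive supplementation, patients with vitamin D deficiency who receive supplementation", and patients with sufficient levels. It closes in the singular: "so the control group will, in effect, receive standard care".
- **Statistical analysis.** "We will compare health gain between groups at baseline and at 6 months". The tests named for continuous or ordinal outcomes in independent groups are Student's t, Welch and Mann-Whitney. Multivariable models, including analysis of covariance, are allowed but are to be used sparingly. No pair of groups is named.
- **Aim.** The question for the future trial is whether supplementation improves outcomes in patients who are deficient.
- **Outcomes.** The primary clinical outcome is worded more loosely, as the effect of vitamin D on health gain. That could mean supplementation or baseline status.

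**The concern.** The Aim asks about supplementation among deficient patients. Only one contrast answers it with the protection of randomisation: deficient patients allocated to supplementation against deficient patients allocated to none. The analysis text never names that contrast. The Control groups section meanwhile gives one control label to two sets of patients, one randomised and one not.

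An analyst with three groups and two-sample tests must choose a pair or collapse three groups into two, and the shared label supplies a ready way to collapse them. The Background reports lower hip and knee scores after surgery in deficient patients. A pooled control group could carry that prognostic difference into what is reported as the effect of vitamin D. The planned comparison of mean post-operative scores would be exposed most directly. For health gain, the size and even the direction of the gap are less certain, because the hip study cited in the Background found lower scores before surgery as well as after.

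**Working it through.** The plan has no figure to reproduce on this point. The total of 100 rests on expected recruitment over 2 months, not on power. What follows shows what pooling would do if it were done.

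**Inputs from the protocol article**
- Total of 100 participants across all three groups (Participant recruitment; Statistical analysis).
- 1:1 allocation, among patients below 50 nmol/L only (Randomisation).
- Significance at p < 0.05 (Statistical analysis), taken here as two-sided.

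**Assumptions**
- P, the share of participants below 50 nmol/L: 30% to 70%. The article gives no value for the trial population. Its nearest figure is more than 50% of adults over 65 in winter and spring (Background).
- g, the true difference in mean health gain, sufficient minus unsupplemented deficient: 0 to 0.5 SD.
- No effect of supplementation, equal SD within each group, no attrition.

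**Step 1: make-up of a pooled control group**

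Arm size = 100P/2. Pooled controls = 100P/2 + 100(1 − P). Never-randomised share w = 100(1 − P) / pooled controls.

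| P | Supplemented | Randomised controls | Sufficient | Pooled controls | w |
|---|---|---|---|---|---|
| 30% | 15 | 15 | 70 | 85 | 70/85 = 82% |
| 50% | 25 | 25 | 50 | 75 | 50/75 = 67% |
| 70% | 35 | 35 | 30 | 65 | 30/65 = 46% |

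**Step 2: bias**

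The pooled control mean exceeds the randomised control mean by w × g, so the estimated effect of supplementation is shifted by −w × g. At P = 50%:
- g = 0: 0
- g = 0.2 SD: 0.67 × 0.2 = 0.13 SD
- g = 0.3 SD: 0.67 × 0.3 = 0.20 SD
- g = 0.5 SD: 0.67 × 0.5 = 0.33 SD

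**Step 3: false-positive rate at P = 50%**

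Standard error = sqrt(1/25 + 1/75) = 0.231 SD. Rejection rate ≈ Φ(wg/SE − 1.96) + Φ(−wg/SE − 1.96).
- g = 0: 5%
- g = 0.3 SD: 0.20/0.231 = 0.866, so Φ(−1.094) + Φ(−2.826) = 0.137 + 0.002 ≈ 14%
- g = 0.5 SD: 0.333/0.231 = 1.443, so Φ(−0.517) + Φ(−3.403) ≈ 30%

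The normal formula ignores the extra spread that mixing two populations adds to the pooled controls. Simulated t tests, which include it, reject in about 9%, 14% and 29% of trials at g = 0.2, 0.3 and 0.5 SD.

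**Step 4: the same check in score points**

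With an assumed gap of 3 points and SD of 9, the bias is 2.5, 2.0 and 1.4 points at P = 30%, 50% and 70%. The normal formula gives rejection rates of 16.5%, 16.1% and 11.4%.

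**Step 5: the randomised contrast**

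Restricting to randomised patients gives about 15 v 15, 25 v 25 or 35 v 35. The contrast is unbiased whatever g is.

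**The case against.** The strongest reply is that no pooled analysis is planned. The section heading is plural, the three groups are listed separately, and the Aim confines the question to deficient patients. The sentences around the shared label deal with conduct (blinding to vitamin D status, not starting supplements), so control subject may describe how patients are managed rather than an analysis set. This stands in part. The randomised comparison is permitted as much as the pooled one, so the fault is an ambiguous definition. A reader might infer that the planned tests are something other than the randomised comparison, but the article does not say so.

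A reader might also infer, from the wording about who does and does not receive supplementation, that patients will be grouped by treatment taken. The article does not support this. That wording is one descriptive sentence. The Randomisation, Intervention group and Post-operative follow-up sections define the arms by randomisation, and no as-treated rule is stated.

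Nor is it right that only two-sample tests are possible, since analysis of covariance and regression are also foreseen.

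A further reply is that a condensed article may leave the primary contrast and analysis set to a fuller document. That would answer a complaint of silence. It does not answer a shared control label that is actually written and that a fuller document would have to override.

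Finally, the consequences are limited. The article says its inference is to inform a future study rather than to draw direct conclusions. It sizes the next trial from observed means and SDs and published minimal important differences, not from the observed effect. That stands, and it lowers the severity.

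**Conclusion.** The concern holds as an ambiguity in a stated definition. Randomised and non-randomised patients carry one control label, and the between-group tests are not tied to the randomised pair, so a confounded pooled contrast is a permitted reading.

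The size depends on pooling, which is permitted but not stated, and on two quantities the article does not give. For a deficient share of 70% down to 30%, 46% to 82% of pooled controls would be non-randomised. At 50% deficient, a gap in health gain of 0 to 0.5 SD means a bias of 0 to 0.33 SD against supplementation and a false-positive rate of 5% to about 29%. The lower end is real: with no gap in gain there is no bias. If sufficient patients gained less, because they start higher, the bias would favour supplementation.

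Severity is moderate. The trial is a feasibility study that disclaims direct inference, but its between-group estimate will be read as the first randomised evidence on this question.

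**What to change.** Change the wording in two sections.

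- **Control groups.** Keep the term control for patients below 50 nmol/L who are allocated to no supplementation. Call patients at or above 50 nmol/L a non-randomised reference cohort. Describe the two deficient groups by allocation. State the 50 nmol/L threshold each time, because the Intervention group section also uses deficiency for levels below 25 nmol/L.
- **Statistical analysis.** Name the main between-group comparison for health gain: deficient patients allocated to supplementation versus deficient patients allocated to none, analysed as randomised. State that the reference cohort is reported separately and is not pooled into control, and that any comparison with it is observational. In the same sentence, correct the reference to health gain at baseline, since Outcomes defines health gain as a difference between pre-operative and post-operative scores.

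No patients, visits or data are added. The main comparison will have fewer patients than a pooled one (25 v 25 instead of 25 v 75 at 50% deficient), but the extra patients in the pooled version are not randomised controls.
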